### Recruitment

Recruitment was conducted for 5 months, from August (the first patient was recruited on August 10, 2021) to the end of December 2021, in cooperation with the multiprofessional team (physicians, physician assistants, clinical psychologists, social workers, and midwives) at the CHC. The eligibility of participants was determined by the CHC staff, who were trained in advance. Based on the inclusion criteria, the staff identified patients with at least 1 chronic diagnosis and then contacted them directly. A recruitment protocol was used. Patients received a letter of information that included notes on the study aims, study design, data protection, and randomization. The information was available in 6 languages—Turkish, Macedonian, Albanian, English, French, and German. Participation is voluntary, and consent can be withdrawn at any time without incurring disadvantages in treatment. In addition, once per week, a nurse (and a bachelor of arts student) supported the recruitment process at the CHC in order to clarify questions. After verbal consent was obtained, patients were contacted by a research assistant by telephone for further information. Questionnaires were designed as self-report surveys and were administered after a 48-hour consideration period and the provision of written consent. If there is a need for assistance, home interviews or interviews at the CHC will be offered by study assistants.

### Assignment of Interventions (for Controlled Trials)

#### Sequence Generation

After the baseline survey, a statistician from the Institute of Medical Biometry and Epidemiology at the Medical Center Hamburg-Eppendorf randomly assigned included study participants to the intervention group or control group (stratified by gender). Randomization was realized via a computer-based permuted block design with variable block lengths to generate the allocation sequence, in which the number of assignments to the intervention group satisfied the 1:1 allocation ratio. The allocation concealment mechanism is described in the next subsection.

#### Data Collection, Management, and Analysis

After randomization, the interventionists were informed about the group assignments because they are the ones who will implement the interventions. This was also necessary for informing the participants about the allocations. The research assistant who is responsible for data extraction and analyses was blinded and excluded from the entire recruitment process.

#### Data Collection Methods

Data will be collected primarily at baseline (t_0_), after 6 months (t_1_), and after 12 months (t_2_). At baseline, data will be collected on the primary and secondary outcomes (described in the *Outcomes* section), in addition to variables on diseases, demographics, socioeconomic factors, the utilization of health services, and digital mobile health apps. The flow of participants through the study phases has been presented in a flow diagram that conforms to the CONSORT (Consolidated Standards of Reporting Trials) guidelines [29] for pragmatic trial reporting (Multimedia Appendix 2).

#### Data Management

Surveys will be realized as paper and pencil assessments. For data input, descriptive statistics and statistical analyses, which will be conducted with SPSS Statistics version 22 (IBM Corporation), will be used. The double entry of data (primary data) has been planned for the first 10 questionnaires, and random checks will be performed as data entry progresses to check for input errors. Collected data from the baseline and follow-up assessments will be checked for missing data, plausibility, and outliers.

### Statistical Analysis

For analyses, data from the intention-to-treat population will be used. Data from the baseline survey will be analyzed descriptively to compare the demographic, socioeconomic, and clinical characteristics of study participants. Means and SDs or medians and IQRs will be calculated for continuous variables, and absolute frequencies and proportions will be calculated for categorical variables. For the primary analysis, a mixed linear regression model will be used, with groups, time points, and gender included as fixed effects; participants included as random effects; and baseline values included as covariates. For the primary analysis, the treatment effect at t_2_ will be evaluated, and the 2-sided significance level (α) will be set to 5%. To summarize the characteristics and outcomes of each group, as well as for the comparison of the groups, descriptive statistics and appropriate tests will be used. For regression models, gender will be included as a fixed effect, as per the stratification used in the randomization process. Other covariates (eg, age and the number and duration of diagnoses of chronic illness) will be included in sensitivity analyses. Following the study analysis procedures of Markle-Reid et al [20], the correlation between the quantity of utilized interventions and the primary outcome will be analyzed.

### Ethics Approval

Ethics approval was obtained from the institutional Competence Health Center’s ethics commission at the University of Applied Sciences Hamburg in March 2021 (procedure number: 2020-14). The study will be conducted in accordance with the commission’s ethical standards and the Helsinki Declaration.

## Results

The RCT was developed to evaluate a community health nurse model for primary care settings. Funding for conducting the CoSta study was provided by the Federal Ministry of Education and Research Germany in 2020 (contract number: 13FH019SX8). In total, 187 participants were recruited at the beginning of August 2021. Further, 92 were excluded and 94 were randomized. Surveys will be conducted until the end of 2022. A summary of the results will be published in peer-reviewed journals and presented at scientific conferences after the completion of the t_2_ surveys (ie, by the end of 2022).

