### Sample Size

A power analysis was done a priori. The sample size was calculated with the Power Analysis & Sample Size 16.0.3 program (NCSS LLC) to demonstrate group differences in the primary outcome (MCS scores). The assumptions were based on a study by Markle-Reid et al [20]. The sample size was estimated based on an effect size of 0.50 with a significance level (α) of .05, using a 2-sided (2-tailed), 2-sample unequal variance *t* test (experimental group sample size: mean 55.3, SD 7.8; control group sample size: 53.5, SD 9.6). The maximum number of cases was limited to 130 in order to guarantee that the interventions will be offered to every participant in the intervention group during the limited study period. This maximum sample size of 130 (65 per group), which was calculated based on the aforementioned input parameters, yields 64.1% power to reject the null hypothesis.

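### The only stated power (64.1%) is for 130 participants, but recruitment closed with 94 randomised; no power is given for 94, the 64.1% cannot be reproduced, and the flow counts differ by one

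*Protocol article*

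**What the plan says.** The Sample Size section of the protocol article bases its calculation on an assumed effect: "The sample size was estimated based on an effect size of 0.50 with a significance level (α) of .05". The test is a two-sided "2-sample unequal variance" t test, and the section prints group values in brackets: "experimental group sample size: mean 55.3, SD 7.8; control group sample size: 53.5, SD 9.6". The total is a ceiling set by capacity: "The maximum number of cases was limited to 130 in order to guarantee that the interventions will be offered" to everyone in the intervention group. The power of 64.1% is attached to that ceiling: "This maximum sample size of 130 (65 per group"). No allowance for dropout is stated.

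The Recruitment section describes enrolment in the past tense, ending in December 2021. The Results section, like the Abstract, reports the outcome: "In total, 187 participants were recruited at the beginning of August 2021" and "Further, 92 were excluded and 94 were randomized". Neither place, nor the Strengths and Limitations section, gives a power or a precision for 94, although the limitations do acknowledge that recruitment was difficult.

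The Statistical Analysis section plans a mixed linear model on the intention-to-treat population, adjusted for baseline and gender, with the treatment effect evaluated at 12 months (t2). For that test, "the 2-sided significance level (α) will be set to 5" percent.

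**The concern.** The article already knew its final randomised number, yet the only power it offers is for a sample it did not reach. A reader who wants to judge what a non-significant or imprecise 12-month result can tell has only the 64.1% to go on. That figure belongs to another sample size and to an unadjusted t test, not to the planned model.

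Two further points affect any restatement. The inputs printed beside the 64.1% have to agree with one another before a recalculation for 94 means anything. And the number randomised defines the intention-to-treat population, so the flow counts should add up.

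**Working it through.** **Inputs.** From the Sample Size section: two-sided α = 0.05, Welch test, effect size 0.50, means 55.3 and 53.5, SDs 7.8 and 9.6, 65 per group, power 64.1%. From the Trial Design section: 1:1 allocation. From Results: 187, 92 and 94. The split of the 94 is not given; I take 47 per arm. The shortfall is 1 − 94/130 = 28%.

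**Do the effect inputs agree?** Root-mean-square SD = √[(7.8² + 9.6²)/2] = 8.75. The printed difference is 55.3 − 53.5 = 1.8 points, so 1.8/8.75 = 0.21 SD. An effect size of 0.50 would be 0.50 × 8.75 = 4.37 points. The two inputs differ by a factor of about 2.4.

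**Reproducing 64.1% at 65 per group.** SE = √(7.8²/n + 9.6²/n), and power comes from the non-central t distribution with Satterthwaite degrees of freedom and non-centrality (difference/SE). At n = 65, SE = 1.534.
- Effect size 0.50: 4.37/1.534 = 2.85, power 80.7%.
- Printed means and SDs: 1.8/1.534 = 1.17, power 21.4%.
- One-sided versions: 88.3% and 31.6%.

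None gives 64.1%. Solving backwards, 64.1% at 65 per group needs a difference of 3.59 points (0.41 SD), a value that appears nowhere in the article.

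**Power for 94.** At n = 47, SE = 1.804. The columns for 42 and 37 per arm correspond to an assumed 10% and 20% of t2 values missing (42.3 and 37.6, rounded down).

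| Difference | 65 per arm | 47 per arm | 42 per arm | 37 per arm |
|---|---|---|---|---|
| 4.37 points (0.50 SD) | 80.7% | 66.9% | 61.9% | 56.4% |
| 1.8 points (printed) | 21.4% | 16.7% | 15.4% | 14.1% |
| 3.59 points (back-solved) | 64.1% | 50.3% | 45.9% | 41.3% |

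The difference detectable with 80% power is 4.33 points at 65 per arm and 5.11 points at 47 (5.11/8.75 = 0.58 SD).

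At effect size 0.50, 47 per arm gives 66.9%, slightly above 64.1%. At 45 per arm it is 65.0% and at 44 per arm 64.0%, so it drops below 64.1% once 3 of 47 are lost (about 6%).

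**Planned model.** Approximate the baseline-adjusted t2 contrast by multiplying the SDs by √(1 − r²), where r is the baseline-to-t2 correlation. The documents give no r; 0.5 to 0.7 is an assumption. At 47 per arm with complete data, power is then 79% to 92% for 0.50 SD and 21% to 28% for 1.8 points. The r at which adjustment offsets the fall from 65 to 47 per arm, relative to an unadjusted test, is about √(1 − 47/65) = 0.53.

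**Flow counts.** 92 + 94 = 186 against 187 recruited; equivalently 187 − 92 = 95, not 94. The Abstract and the Results carry the same three numbers.

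**The case against.** The article does not claim 64.1% for 94. It calls the analysis a priori, ties the figure to the maximum of 130, and reports 94 openly. The 130 is a capacity limit, so 94 does not miss a target derived from a power goal. All of this stands. What remains is that the figure is left without qualification next to a closed recruitment that it does not describe.

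A reader might infer that the trial now has less than 64.1% power on any reading of its assumptions. The documents do not support that: at the named effect size of 0.50 with complete data, 94 gives 66.9%, and baseline adjustment could raise it. A reader might also infer that 64.1% was right for 130 and is merely out of date. It cannot be reproduced at 130 either.

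That the 64.1% assumes complete 12-month data is an inference from silence on dropout, not something the article writes. The 10% and 20% losses above are likewise assumptions.

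On the counts, it is tempting to conclude that a randomised participant has been lost from the intention-to-treat set. Nothing shows this. Any of the three numbers could be off by one, or one person could have been neither excluded nor randomised, since allocation followed the baseline survey. The flow diagram in Multimedia Appendix 2 is not shown and may settle it.

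Finally, the article nowhere proposes to read a non-significant result as absence of effect, so no rule on that is called for here.

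**Conclusion.** The point holds in this form: the sole stated power belongs to 130 participants, the article itself reports 94 randomised, and no power is given for 94. The cost of the smaller sample at fixed inputs is about 14 percentage points at 0.50 SD (80.7% to 66.9%), about 5 at 1.8 points (21.4% to 16.7%), and about 14 at the back-solved difference (64.1% to 50.3%). These figures rest on an unadjusted Welch test, an even split of the 94 and complete data.

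The conflict between 0.50 and 0.21 SD matters more than the shortfall. Depending on which input is meant, unadjusted power for 94 is 66.9% or 16.7%, so the effect size must be settled first. Whether the planned model restores the loss depends on a baseline correlation that the article does not give. The count discrepancy is one person and minor, but it touches the analysis denominator.

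**What to change.** In the Sample Size section:
1. Reconcile the effect size of 0.50 with the printed means and SDs, and say which difference in mental component summary score the trial is judged against.
2. State that 64.1% does not apply to the randomised sample, and either show the inputs that produce it at 130 or withdraw it.
3. Give power and detectable difference for the 94 randomised, using the actual split, under the planned baseline-adjusted t2 contrast. Show it over stated ranges of missing t2 data and of baseline correlation, marked as assumptions.

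In the Abstract and Results, reconcile 187, 92 and 94 with the flow diagram and correct whichever count is wrong, or account for the remaining person.

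The cost is one recalculation and some wording. No further enrolment and no change to the primary analysis are needed. The stated figure may turn out less favourable.

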## Discussion

### Study Overview

The CoSta study will evaluate a community health nurse–led intervention for enhancing the well-being of patients with chronic health conditions in an urban neighborhood. By using a randomized trial design, the feasibility and benefits of the CoSta intervention will be compared to those of usual treatment. Thus, the study will focus on advanced nursing practitioners’ role in Germany and will offer an approach to targeting the needs-oriented care of patients with chronic illnesses.

Via a randomized group comparison, the analyses will generate data on health-related quality of life, depressive symptoms, anxiety, health literacy, coping, and the utilization of health care in the study population. Furthermore, influencing social aspects and local contexts will be taken into consideration.

The study results could contribute to informing stakeholders in the health care system about responsibilities that can be applied universally in primary care. The expected results could reduce the research-to-practice gap, and they could serve as a basis for the transfer the care model to other regions and the German health care system.

### Strengths and Limitations

A strength of the CoSta study and the nurse-led model is the integration of a multiprofessional team within the CHC. Additionally, the study design can be applied directly in the field. The study will be conducted with the cooperation of the study participants. The CoSta study will provide evidence-based information about a new approach in health care for providing a better quality of life to patients with (multiple) chronical illnesses in a more socially disadvantaged neighborhood. The study results can be used to support other ongoing projects [13,14] that target the anchoring of CHN in Germany.

Due to the field conditions however, there are limitations that can be expected throughout the study period. First, there will probably be a greater need for trained staff during the entire study period. Particularly for the recruitment and education of study participants before study enrollment, the study nurse was a supportive team member for recognizing barriers at an early stage. Second, due to the global COVID-19 pandemic, it was difficult to identify and recruit patients with chronic illnesses. As such, a longer period for recruitment would have been useful.

### Harms

The participants are a vulnerable group due to their chronic health conditions. As experienced nurses, the researchers involved will be able to engage appropriately with the patients, manage spontaneous adverse events, and terminate participation (if necessary). For participants, there will be opportunities to ask questions before and during the data collection process and trial interventions.

## Appendix

Multimedia Appendix 1 Schematic diagram of the Community Health Nursing in der Stadt study phases, as recommended by the SPIRIT (Standard Protocol Items: Recommendations for Interventional Trials) guidelines.

Multimedia Appendix 2 Flow diagram of progress from enrollment to analysis (CONSORT [Consolidated Standards of Reporting Trials] 2010 flow
diagram).

## Abbreviations

CHC: community health center
CHN: community health nursing
CONSORT: Consolidated Standards of Reporting Trials
CoSta: Community Health Nursing in der Stadt
HLS-EU-Q16-GER: short form of the German version of the European Health Literacy Survey Questionnaire
HLS-EU-Q47: European Health Literacy Survey Questionnaire
MCS: mental component summary
RCT: randomized controlled trial
SF-36: 36-Item Short Form Health Survey
SPIRIT: Standard Protocol Items: Recommendations for Interventional Trials
